### Interim analyses {21b}

Interim analyses will not be planned in this study. The intervention in this study is mobile messaging with no unacceptable adverse effects, so there is no need to terminate the trial earlier.

### Methods for additional analyses (e.g., subgroup analyses) {20b}

Subgroup analyses will not be applied in this study.

### Methods in analysis to handle protocol non-adherence and any statistical methods to handle missing data {20c}

The non-adherence of study participants will be recorded (e.g., crossing over to the other randomized group or registering another oral health promotion project). The reasons for withdrawal will also be asked and recorded. Intention-to-treat (ITT) approach will be used for data analysis.

In cases with missing data (particularly for the questionnaire), telephone calls or text messages will collect the missing information. If failed, the data imputation will perform using the mean/mode of the variable from the same group of participants if the missing data is less than 20%. If there is missing data in the follow-up, the last observation carried forward method will be adopted. If 20% or more of the data is missing, then the case will be excluded from the data analysis. The sensitivity analyses will perform to see how great is the impact of missing data and how different data imputations may affect results.

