## Outcomes {12}

The primary outcome will be dental caries increment (by tooth level). The students will be examined at the schools at baseline, 1-year, and 2-year follow-up. Dental caries assessment will base on the ICDAS criteria (International Caries Detection and Assessment System), which will be used to assess both non-cavitated (codes 1 and 2) and cavitated caries lesions (codes 3–6) [16]. The examiners will examine occlusal, mesial, distal, buccal, and lingual surfaces of each tooth.

The secondary outcomes will be:i)Gingival status measured by the percentage of sites with gingival bleeding (BOP%), as recommended by the WHO for conducting oral health surveys [1];ii)Oral hygiene status using the Visible Plaque Index (VPI). The percentage of plaque on the buccal and lingual surfaces of all indicated teeth will be recorded [1];iii)Average frequency of toothbrushing per day (2 times as preferred);iv)Average frequency of intake of sugary snacks/drinks per day (2 times or less frequent as preferred);v)Average amounts of free-sugar intake per day (<25 g as preferred); andvi)Oral health self-efficacy on behaviors (questionnaire score rated on a 4-point Likert scale, e.g., 1 = not confident at all to 4 = very confident)

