## Data collection and management

### Plans for assessment and collection of outcomes {18a}

The data collection will involve oral examination and questionnaire surveys. Students will have oral examinations at school at baseline, 1-year, and 2-year follow-up by one or two trained, experienced, and calibrated examiner(s). An intra-oral LED light, disposable mouth mirrors, and WHO dental probes will be used during the clinical examination. No x-ray will be taken. Inter-examiner and intra-examiner reliability will be assessed.

Self-completed questionnaires will be delivered to the students at baseline, 6 months, 1-year, and 2-year follow-up through the schools. The items in a validated oral health behavior questionnaire for adolescents based on the health belief model (OHBQAHBM) will be used [22].

Information on the social-demographic backgrounds of the family will also be collected.

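### Carrying the last examination forward scores missed follow-up as caries-free in a cumulative primary outcome, and the 20% exclusion contradicts the stated intention-to-treat analysis

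*Protocol article*

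**What the plan says.** The missing-data section {20c} makes four statements that bear on one another.

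- Analysis population: "Intention-to-treat (ITT) approach will be used for data analysis".
- Below 20% missing, once telephone or text retrieval has failed: "the data imputation will perform using the mean/mode of the variable from the same group of participants". The section mentions the questionnaire as the main case but does not exempt the clinical data.
- Missed follow-up: "If there is missing data in the follow-up, the last observation carried forward method will be adopted".
- At or above the threshold: "If 20% or more of the data is missing, then the case will be excluded from the data analysis".

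It then promises sensitivity analyses on the impact of missing data and of different imputations, without naming them.

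Outcomes {12} makes the caries increment at tooth level primary, and Sample size {14} sizes it as new carious teeth (∆DMFT) over 24 months. On timing, {12} says "The students will be examined at the schools at baseline, 1-year, and 2-year follow-up". For the questionnaire, {18a} says "Self-completed questionnaires will be delivered to the students at baseline, 6 months, 1-year, and 2-year follow-up through the schools". The statistical methods section {20a} specifies a three-level random-intercept mixed model with time, student and school as levels. Section {20c} does not say how its rules fit with that model.

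**The concern.** DMFT counts decayed, missing and filled teeth, so it accumulates. Carrying a score forward does not hold a stable quantity constant. It assigns zero new caries to the unobserved period, which is the best possible result. A student last seen at baseline gets a two-year increment of zero, and a student last seen at one year gets nothing for the second year. The estimated effect then depends partly on who stopped attending.

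The exclusion rule raises a different problem. It removes students from randomised schools because of something that happens after allocation, in the same section that promises intention-to-treat. Because the 20% has no stated denominator and the rules have no stated order, the text does not settle whether a student who misses the two-year examination is carried forward or dropped. The primary analysis set would then be open to choice after the data are seen.

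**Working it through.** **1. The plan's own figures.** From Sample size {14}: effect size 0.21, three groups, 5% significance, 80% power. One-way ANOVA power from the noncentral F gives 74 per group (power 0.801). Design effect = 1 + (75 − 1) × 0.03 = 3.22. Then 74 × 3.22 = 238.3 and 238.3 / 0.90 gives 265, which four schools of 75 round up to 300. These figures reproduce and are not in dispute. The planned difference is 0.34 − 0.12 = 0.22, with SD about 0.50 and dropout 10%.

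**2. Carry-forward with equal dropout.** Let d be the dropout proportion and a the share of the two-year increment already accrued at the last examination. Expected increment = true increment × [1 − d(1 − a)]. Take a = 0 when baseline is carried and a = 0.5 when year 1 is carried. Linear accrual and dropout unrelated to caries are assumptions.

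| Dropout, both arms | Baseline carried | Year 1 carried |
|---|---|---|
| 10% (plan) | 0.306 − 0.108 = 0.198 | 0.323 − 0.114 = 0.209 |
| 20% (assumed) | 0.272 − 0.096 = 0.176 | 0.306 − 0.108 = 0.198 |

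At the planned dropout the effect is diluted by 5% to 10%.

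Pairwise power (normal approximation, SD held at 0.50, no correction for the small number of schools):
- With 300 filled-in students per arm, effective n = 300 / 3.22 = 93.2. Power is 0.81 at a difference of 0.209 and 0.77 at 0.198.
- With only the 270 observed students and the undiluted 0.22, the design effect is 1 + 66.5 × 0.03 = 2.995 and effective n = 90.2. Power is 0.84.

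**3. Carry-forward with unequal dropout (15% against 5%, assumed).**
- No true effect, 0.34 in both arms: baseline carried, 0.34 × 0.95 − 0.34 × 0.85 = 0.034; year 1 carried, 0.34 × 0.975 − 0.34 × 0.925 = 0.017. The difference favours the arm with more dropout, whichever that is.
- Planned effect present, control arm losing 15%: 0.289 − 0.114 = 0.175 (baseline) or 0.3145 − 0.117 = 0.1975 (year 1).
- Planned effect present, test arm losing 15%: 0.323 − 0.102 = 0.221 or 0.3315 − 0.111 = 0.2205.

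**4. Overlap of the rules.** There are three examinations and four questionnaires. One missed examination is 1/3 = 33% and one missed questionnaire is 1/4 = 25%. If the 20% is counted by visit within each instrument, every missed visit leads to exclusion and carry-forward never operates. If it is counted over items, variables or participants, a missed two-year examination may instead be carried forward. The text does not choose.

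**5. Same-group mean imputation.** With a fraction m filled by the arm mean, the sample SD shrinks by √(1 − m), while the true standard error is based on n(1 − m) values. Naive SE / true SE = √(1 − m) × √(1 − m) = 1 − m. A nominal 5% test then has type I error 2[1 − Φ(1.96(1 − m))]: 7.8% at m = 10% and 11.2% at m = 19%. Simulation of two arms of 300 independent values gave 7.5% and 11.4%.

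**The case against.** **The rules cannot all do harm at once.** A reader might infer that a missed two-year examination, being 33% of the examinations, triggers both carry-forward and exclusion. The document does not support that. The 33% exists only if examinations are the denominator, and an excluded student is not carried forward. A natural reading is that the 20% limit governs incomplete forms and carry-forward governs missed visits. This stands: the supportable criticism is that scope and order are undefined. Each reading still leaves a fault, either zero increments for absent students or a departure from intention-to-treat. A fuller analysis plan could supply the denominator and order, but the article itself fixes both rules.

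**Mean or mode imputation is not aimed at caries.** It follows telephone or text retrieval, which cannot recover an oral examination. A reader might also infer that it exaggerates the difference between arms. If data are missing completely at random it does not bias the arm mean; its main fault is too small a standard error.

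**The mixed model does not make every rule redundant.** That inference is tempting but wrong. The model does not fill missing covariates such as parental education, nor missing items in the self-efficacy score. If the increment itself is the response, a student with no follow-up examination contributes nothing.

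**The size is modest.** With equal dropout carry-forward is conservative, and 0.198 requires all losses before year 1. The 15% against 5% imbalance is not in the document: the Discussion expects that non-attendance could rise, not that it would differ by arm. The standard error of a pairwise difference is about 0.50 × √(2 × 3.22 / 300) = 0.073, so 0.034 is under half of one. All this stands. Still, participants are unmasked and contact differs markedly between arms, so imbalance cannot be ruled out.

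**Other mitigation.** Sensitivity analyses are promised, but they are unnamed and do not decide the primary rule. If non-cavitated ICDAS lesions count towards the increment, some may reverse and the accumulation argument weakens; the measure used for sizing is nevertheless ∆DMFT.

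**Conclusion.** The point holds in this form. Carry-forward is the wrong stated rule for an accumulating increment. It costs about 5% to 10% of the planned difference at 10% equal dropout, assuming linear accrual and dropout unrelated to caries. It is not reliably conservative: under an assumed 15% against 5% imbalance and no true effect it creates 0.017 to 0.034, or 8% to 15% of the 0.22 target, in favour of the arm losing more students. A reader might infer that such a bias is to be expected in this trial; the document gives no dropout by arm, so it is a possibility only.

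Exclusion at 20% contradicts the intention-to-treat statement regardless of any numbers, and the undefined denominator and order leave the primary analysis set open. Same-group imputation is a lesser fault, mainly in the questionnaire outcomes, where the nominal 5% error rate rises to about 8% at 10% missing and about 11% at 19%.

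**What to change.** - **Primary caries outcome.** Delete carry-forward and the 20% exclusion. Analyse all students in the arm allocated to their school, using the three-level mixed model of {20a} with the caries score at every observed visit, including baseline, as the response. The arm-by-time contrast at two years then gives the increment. Allocation is released only after baseline data collection, so students lost later still enter with a baseline score. This relies on missing at random. The alternative is multilevel multiple imputation that includes school, arm, baseline caries and 1-year caries.
- **Covariates and questionnaire items.** Replace group mean or mode with multiple imputation.
- **Sensitivity analyses.** Name them: keep carry-forward or another simple imputation here only, and add a missing-not-at-random check, such as shifting the imputed increments by a stated amount in one or more arms.

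The cost is revised wording in {20c} with a cross-reference to {20a}, and modest analysis time. Neither the sample size nor data collection changes.

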### Plans to give access to the full protocol, participant level-data and statistical code {31c}

The protocol will grant access to the DataHub, a library e-platform of The University of Hong Hong when the completion of the study.

## Oversight and monitoring

### Composition of the coordinating center and trial steering committee {5d}

The principal investigator and an expert in dental public health in our research team will be responsible for coordination with different study sites. They will monitor recruitment rate, and follow-up rates and deal with any problems that deviate from the protocol.

The research investigators comprise the trial steering committee, to monitor and supervise the study’s progress toward its interim and overall objectives. Any amendments to the protocol where appropriate, presentations of results, and data release will be consented to by the committee. The funding agency and IRB will be informed about the mentioned actions through principal investigator reporting.

### Composition of the data monitoring committee, its role and reporting structure {21a}

A Data Monitoring Committee (DMC) will not be considered as this study is about low-risk preventive interventions. The principal investigator will be responsible for the data monitoring and complying with the reporting requirements to the funding agency and IRB. The reporting includes the expected and actual recruitment numbers, dropout rates, and any adverse events.

### Adverse event reporting and harms {22}

Adverse events and other unintended effects of trial interventions will be reported to the funding agency and IRB biannually.

### Frequency and plans for auditing trial conduct {23}

The principal investigator will report the progress of the trial conducted regularly and the final research findings to the funding agency and IRB.

### Plans for communicating important protocol amendments to relevant parties (e.g., trial participants, ethical committees) {25}

All the proposed protocol amendments will be discussed and agreed upon by all the investigators, approval will be obtained from both the funding agency and IRB. The information will be updated in the trial registry as well. The trial participants will also be informed and consent.

### Dissemination plans {31a}

Supposing the results are favorable in showing our student participants who received family-integrated HBM-based messages would have better oral health-related behaviors and better oral health outcomes, we would like to disseminate the results to:i)Department of Health, the Hong Kong Government. The study results will provide much-needed evidence for further developing and implementing a new oral health promotion strategy for adolescents, helpful for the Hong Kong government to re-visit the dental public health policies on adolescents and translate them into practice.ii)Local dental professional bodies (Hong Kong Dental Association, Hong Kong Society of Pediatric Dentistry) and local medical institutions with pediatricians, medical practitioners, and nurses working in adolescent health care.iii)Education Bureau and secondary schools. Effective oral health education could be disseminated through school internet platforms. It creates an opportunity for interdisciplinary partnerships with dental professionals and educational professionals, and we hope to explore a feasible and cost-effective strategy by the linkage of schools, students, and families.

By interim and final reporting, the research findings will be presented at international dental conferences and published in international peer-reviewed journals.

## Discussion

The population-based oral health survey in Hong Kong [23] has shown that 23% of 12-year-old children in Hong Kong had caries experience. Although the extent/severity of caries was low (mean DMFT 0.4), most 12-year-old children (86%) had gingivitis, and calculus was prevalent (64%). The lower prevalence of caries among the Hong Kong adolescent population is associated with the School Dental Care Service provided by the Department of Health, which includes a range of preventive and basic dental care for grade 1 to 6 primary school children. However, School Dental Care Service is not available to secondary school students. Additionally, this survey [23] has shown that 32% of the adolescents did not brush their teeth twice per day and that 36% snacked twice per day or more often. We also found that the oral health status worsened from childhood to early adulthood following a cohort of 638 students from 12 to 18 years old in Hong Kong [24]. Hence, there is a strong need to deliver oral health education among this specific age group, highlighting the significance of this proposed project.

For improving oral health in adolescents, this study would be a first step towards the mobile-health-associated Sustainable Development Goals by the WHO [25], as there are no mHealth-driven oral health activities among adolescents in Hong Kong. For there is no governmental oral health service to secondary school students, we hope such a simple intervention using modern-day technology may facilitate positive health behaviors among adolescents, which benefit them for a lifetime.

The innovation of this trial is the combination strategies which is still controversial about the effectiveness of two levels of influence in socio-ecological models (individual and family). Besides, the intervention is theoretically informed, drawing from a behavioral theory from the social-psychological field.

The limitation of this study is the person who can receive the message via smartphone will be recruited, without covering the poor communities with no smartphones. There is a concern about generalizability. Besides, the participants are limited to the cohort of youth in school, therefore the outcomes could not be generalized to the out-of-school adolescents as there could be potential peer effects in our study participants.

The potential pitfall in this proposed study would be that dental examinations could not be conducted at schools due to the COVID-19 pandemic. The participants will have a follow-up at the teaching hospital of the Faculty of Dentistry, The University of Hong Kong. This situation may result in a higher rate of non-attendance and decrease the power of the study. We currently estimate the drop-out rate as 10% for the outcome. To make sure enough sample size is reached, we will assess the attendance rates at the dental hospital for all groups as early as practicable to give a reasonable estimation, and try to arrange future dental examinations in the schools when possible depending on the COVID-19 situation at that time.

## Trial status

ClinicalTrials.gov Identifier: NCT05448664. First posted and registered on 7 July 2022. Recruitment will begin in December 2022 and end in June 2023. The project is anticipated to end in June 2025.

## Data Availability

The final trial dataset will be uploaded to DataHub, the University of Hong Kong for public access by the completion of the study.

## Abbreviations

AAPD: American Academy on Pediatric Dentistry
BOP: Bleeding on periodontal Probing
DMC: Data Monitoring Committee
DMFT: Decayed, Missing due to caries, and Filled Teeth in the permanent teeth
GAS: Goal Attainment Scaling
HBM: Health Belief Model
ICC: Intracluster Correlation Coefficient
ICDAS: International Caries Detection and Assessment System
IRB: Institutional Review Board
ITT: Intention-to-treat
mHealth: mobile Health
OHBQAHBM: Oral Health Behavior Questionnaire for Adolescents based on Health Belief Model
OHE: Oral Health Education
VPI: Visible Plaque Index
WHO: World Health Organization
